**Introduction**

Lactating women and their offspring are at risk of vitamin D deficiency. Vitamin D supplementation at a dose of 400 IU/d is not sufficient for lactating women, and higher doses are required (up to 2000 IU/d). Vitamin D supplementation at a dose of 4000-6000 IU/d during lactation was safe for both lactating women and their offspring. However, the safety of such high doses has only been proved in studies with a small number of participants. The safety and effectiveness of vitamin D supplementation at doses higher than 400 IU/d have not yet been studied in Polish lactating women. A high incidence of vitamin D deficiency in pregnant and lactating women and their offspring has been reported. An appropriate vitamin D intake is a fundamental issue because of the role of vitamin D, not only in calcium and bone homeostasis, but also in many other physiological functions. Vitamin D may have an influence on the musculoskeletal system (body composition parameters and interactions between them).

**Aim of the study**

We aim to prospectively compare the influence of vitamin D supplementation (400 IU/d vs. 1200 IU/d) on the vitamin D status, bone mass and body composition of lactating women and their offspring, taking safety issues into account. Additionally, we want to prove that vitamin D supplementation at a dose of 400 IU/d is sufficient to build up an appropriate vitamin D status in breastfed infants, irrespective of maternal vitamin D supplementation (up to 1200 IU/d). We also aim to assess the influence of the season of delivery on the maternal and newborn’s vitamin D status.

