**Methods**

This is a prospective double-blind randomized control trial. Intervention in mothers will last for 6 months. Lactating mothers will be randomly allocated to two groups with different vitamin D intakes.

Group 1 – Maternal vitamin D supplementation at a dose of 400 IU/d (multivitamin tablet containing 400 IU of cholecalciferol + placebo),

Grupa 2 – Maternal vitamin D supplementation at a dose of 1200 IU/d (multivitamin tablet containing 400 IU of cholecalciferol + 800 IU of cholecalciferol),

All infants will receive 400 IU/d of vitamin D3 (1 capsule or 1 drop) throughout breastfeeding, according to the Polish recommendation.

The following assessments are planned during the study:

- Maternal and infants’ data (gestational age, birth weight, Apgar score, vitamin D intake from diet and supplements, educational/socioeconomic status, duration of sunlight exposure, usage of sun blockers)
- Anthropometric measurements (weight, height/length, maternal BMI)
- Assessment of vitamin D status (measurement of serum 25 hydroxyvitamin D (25-OHD) and serum parathormone (PTH))
- Assessment of biochemical signs of vitamin D overload (serum calcium, urinary calcium and creatinine (urinary calcium /creatinine ratio)).
- Assessment of bone status (total body and lumbar spine bone mineral content (TB BMC L1-L4 BMC), total body and lumbar spine bone mineral density (TB BMD, L1-L4 BMD) by dual energy X-ray absorptiometry
- Assessment of body composition (lean body mass (LBM) and fat mass (FM)) by dual energy X-ray absorptiometry
- Statistical analysis (distribution analysis, Student’s T test for normally and U-Mann-Whitney test for non-normally distributed variables, chi^2^ test for categorical variables, Pearson or Spearman correlation, one-way analysis of variance or Friedman ANOVA test). *P*-values <0.05 were considered significant.

*Schedule of study visit*

Baseline assessment (before introduction of vitamin D supplementation) will provide baseline characteristics of the studied participants. Cord blood samples will be collected at delivery. Maternal baseline blood samples will be collected within 3 weeks after delivery when maternal and infants’ DXA measurements will be performed. Follow–up visits will take place at the 3^rd^ and 6^th^ month after delivery.

Biochemical measurements in serum will be performed by fully automatic methods to minimize collected blood volume at 2ml.

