**Theoretical results**

- Confirmation of the hypothesis that maternal vitamin D supplementation at a dose of 1200 IU/d is more efficient than 400 IU/d for lactating women, and safe for both mother and child, and positively changes bone mass and body composition (better ratio between muscle and fat components)
- Verification of a maternal need for vitamin D supplementation during lactation and modification of current recommendations
- Confirmation of the effectiveness of vitamin D supplementation at the currently recommended dose in breastfed infants
- Confirmation of the hypothesis that the season of delivery has an influence on maternal and newborn vitamin D status, and if so, a change in the currently recommended vitamin D supplementation according to season.

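### The aim of proving that 400 IU/d suffices in infants whatever the mother takes cannot be met by the listed difference and association tests at P<0.05

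*Protocol*

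**What the plan says.** Protocol, Aim of the study, has two parts that bear on infants. The leading sentence compares maternal 400 with 1200 IU/d for their effect on the status of the women and of their offspring. The next sentence adds: "Additionally, we want to prove that vitamin D supplementation at a dose of 400 IU/d is sufficient" for an appropriate status in breastfed infants, "irrespective of maternal vitamin D supplementation (up to 1200 IU/d"). Theoretical results lists as an expected outcome "Confirmation of the effectiveness of vitamin D supplementation at the currently recommended dose in breastfed infants".

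Patients gives 150 mother-infant pairs. Methods randomises the mothers to two groups and gives every infant 400 IU/d.

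The statistical analysis item in Methods names Student's "T test for normally and U-Mann-Whitney test for non-normally distributed variables", then the chi-square "test for categorical variables, Pearson or Spearman correlation, one-way analysis of variance or Friedman ANOVA test". Its only decision criterion is that P-"values <0.05 were considered significant".

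The protocol gives no 25-OHD level or proportion of infants that would count as appropriate, no margin for the between-arm difference, and no confidence-interval criterion.

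**The concern.** The aim is worded as something to be proved, and it has two components: infants reach an appropriate status, and they do so in both maternal arms. The protocol pairs it with tests that can only reject a hypothesis of no difference or no association. Rejection in a between-arm test would show that maternal dose matters, but not whether either arm is adequate. Non-rejection would show neither adequacy nor absence of a maternal effect, and it becomes more likely as pairs are lost or measurements get noisier.

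The design offers no other route. Every infant receives the same dose, so there is no randomised infant comparator, and sufficiency can be judged only against a stated level. The protocol intends its results to inform recommendations, so a conclusion on the infant dose without a criterion behind it would carry weight that the analysis cannot support.

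**Working it through.** **1. What each listed method can show about the infant aim**

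| Method | Null hypothesis | Shows adequacy in each arm? | Shows that maternal dose is irrelevant? |
|---|---|---|---|
| t test, Mann-Whitney | no between-arm difference | no | no |
| chi-square | no association of category with arm | no | no |
| Pearson, Spearman | no association | no | no |
| one-way ANOVA, Friedman | no difference between groups or visits | no | no |

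A significant rise between visits would show change, not that an appropriate level was reached.

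**2. Adequacy and similarity are separate questions**

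- Both arms adequate but clearly different: the sufficiency claim is true, and a difference test rejects.
- Both arms equally deficient: the claim is false, and a difference test does not reject. An equivalence test could even succeed.

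So no between-arm result, of either kind, settles sufficiency.

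**3. How little a non-significant result says**

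Inputs: 150 pairs (Patients) and the 0.05 level (Methods). Assumed, because the protocol does not state them: equal allocation (75 per arm), two-sided testing, 60 and 50 per arm as attrition scenarios, and true differences of 0.2 to 0.4 SD. The protocol has no power figure to reproduce. Normal approximation throughout, in SD units.

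Standard error of the difference = √(2/n): 0.163 for n = 75 and 0.200 for n = 50. The 95% half-width = 1.96 × SE: 0.32 SD and 0.39 SD.

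Power ≈ Φ(d/SE − 1.96). For d = 0.3:

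- n = 75: 0.3/0.163 = 1.84, and Φ(−0.12) = 0.45, so 55% are non-significant.
- n = 50: 0.3/0.200 = 1.50, and Φ(−0.46) = 0.32, so 68% are non-significant.

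Probability of a non-significant result:

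| True difference | 75 per arm | 60 per arm | 50 per arm |
|---|---|---|---|
| 0.2 SD | 77% | 81% | 83% |
| 0.3 SD | 55% | 62% | 68% |
| 0.4 SD | 31% | 41% | 48% |

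For a categorical endpoint, with assumed proportions adequate of 90% and 80% and 75 per arm: pooled SE = √(2 × 0.85 × 0.15/75) = 0.058, unpooled SE = √((0.09 + 0.16)/75) = 0.058, and power = Φ((0.10 − 1.96 × 0.058)/0.058) ≈ 0.40. About 60% of such trials would show no significant difference.

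**4. What a margin would need**

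Two one-sided 5% tests, true difference zero, 80% power: margin = (1.645 + 1.282) × √(2/n).

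- n = 75: 2.927 × 0.163 = 0.48 SD.
- n = 50: 2.927 × 0.200 = 0.59 SD.

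The 90% half-width at 75 per arm is 1.645 × 0.163 = 0.27 SD, but a margin only slightly wider is of little use. At 0.30 SD the estimate must fall within 0.30 − 0.269 = 0.031 SD of zero, that is 0.031/0.163 = 0.19 standard errors, which has probability of about 15%.

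**5. What a per-arm interval would deliver**

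For an assumed observed 90% adequate, the simple 95% half-width is 1.96 × √(0.9 × 0.1/n): 6.8 percentage points for n = 75 (lower limit about 83%) and 8.3 for n = 50 (lower limit about 82%). A per-arm criterion can therefore be assessed with the planned numbers, depending on the level required.

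**The case against.** The strongest objection is that the sentence makes no claim of equal status between arms. What is to be proved is sufficiency, the reference to maternal dose only says that it should hold in either arm, and Theoretical results restates the expectation without mentioning maternal dose. This stands. A reader might infer a pure no-difference claim and ask for an equivalence test in place of the difference test. The documents do not support that. Equivalence alone could succeed with both arms deficient, and the leading aim explicitly compares the two doses in offspring, so the difference test has a proper job.

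A reader might also infer that the investigators will treat P≥0.05 as proof. No section says so. The test list is not assigned to particular aims, and the rule speaks only of what counts as significant. The point is that the stated analysis contains no valid route to the stated conclusion, not that a misuse is planned.

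Two further objections have partial force. The aim is introduced as an addition, so it is not shown to be a principal one. And a separate statistical analysis plan might supply a cut-off or margin. But the protocol itself states the aim, the tests and the decision criterion, and as stated these do not fit together.

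**Conclusion.** The point holds in a limited form: a supplementary aim worded as proof is paired with analyses that cannot establish it. This is so whether the sentence is read as sufficiency in each arm (the better reading) or as no effect of maternal dose.

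The mismatch follows from the text alone. The figures show only its size for the between-arm part: with an assumed 75 infants per arm, a true 0.3 SD difference is non-significant about 55% of the time, rising to 68% with 50 per arm. These rest on assumed equal allocation, two-sided testing, attrition and effect sizes. They are not the probability of proving a false claim, because a 0.3 SD difference between arms does not by itself make sufficiency untrue.

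**What to change.** Keep the between-arm difference test for the comparative aim. For the infant aim, add to the protocol or the statistical analysis plan, before unblinding:

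- **Sufficiency.** A confidence interval in each maternal arm for the proportion of infants with appropriate 25-OHD (or for the mean), judged against a cut-off and a required level chosen by the investigators. Claim sufficiency irrespective of maternal dose only if both arms meet it.
- **Maternal dose.** The between-arm estimate with its confidence interval. State that maternal dose makes no difference only if the 90% interval lies inside a pre-stated margin chosen on clinical grounds. Check first that the margin is attainable: about 0.48 SD is needed for 80% power at a true difference of zero with 75 per arm, and about 0.59 SD with 50.

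If no such criterion is acceptable, change the verb in the aim from prove to estimate, and soften the matching line in Theoretical results.

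The cost is wording plus the choice of a cut-off, a required level and, if wanted, a margin. The data are the same. The downside is that the infant claim may end as inconclusive, and for the no-difference statement this is likely if the clinically acceptable margin is well below 0.48 SD.

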**Patients**

150 lactating mother-infant pairs.

*Inclusion criteria*

Healthy women, declaring breastfeeding for 6 months.

Breastfed term newborns without major medical problems.

*Exclusion criteria*

Maternal diabetes, maternal endocrine disorders during pregnancy, multiple gestation.

Liver diseases and cholestasis, renal insufficiency, endocrine disorders, congenital malformations and anticonvulsant treatment in neonates.

**Methods**

This is a prospective double-blind randomized control trial. Intervention in mothers will last for 6 months. Lactating mothers will be randomly allocated to two groups with different vitamin D intakes.

Group 1 – Maternal vitamin D supplementation at a dose of 400 IU/d (multivitamin tablet containing 400 IU of cholecalciferol + placebo),

Grupa 2 – Maternal vitamin D supplementation at a dose of 1200 IU/d (multivitamin tablet containing 400 IU of cholecalciferol + 800 IU of cholecalciferol),

All infants will receive 400 IU/d of vitamin D3 (1 capsule or 1 drop) throughout breastfeeding, according to the Polish recommendation.

The following assessments are planned during the study:

- Maternal and infants’ data (gestational age, birth weight, Apgar score, vitamin D intake from diet and supplements, educational/socioeconomic status, duration of sunlight exposure, usage of sun blockers)
- Anthropometric measurements (weight, height/length, maternal BMI)
- Assessment of vitamin D status (measurement of serum 25 hydroxyvitamin D (25-OHD) and serum parathormone (PTH))
- Assessment of biochemical signs of vitamin D overload (serum calcium, urinary calcium and creatinine (urinary calcium /creatinine ratio)).
- Assessment of bone status (total body and lumbar spine bone mineral content (TB BMC L1-L4 BMC), total body and lumbar spine bone mineral density (TB BMD, L1-L4 BMD) by dual energy X-ray absorptiometry
- Assessment of body composition (lean body mass (LBM) and fat mass (FM)) by dual energy X-ray absorptiometry
- Statistical analysis (distribution analysis, Student’s T test for normally and U-Mann-Whitney test for non-normally distributed variables, chi^2^ test for categorical variables, Pearson or Spearman correlation, one-way analysis of variance or Friedman ANOVA test). *P*-values <0.05 were considered significant.

*Schedule of study visit*

Baseline assessment (before introduction of vitamin D supplementation) will provide baseline characteristics of the studied participants. Cord blood samples will be collected at delivery. Maternal baseline blood samples will be collected within 3 weeks after delivery when maternal and infants’ DXA measurements will be performed. Follow–up visits will take place at the 3^rd^ and 6^th^ month after delivery.

Biochemical measurements in serum will be performed by fully automatic methods to minimize collected blood volume at 2ml.

A single dual energy X-ray absorptiometry measurement will be performed at every visit for assessment of bone status and body composition, to minimize the radiation dose at 5 μSv (for comparison, the radiation dose for spinal X-ray is 500-900 μSv, and for a transatlantic flight, 60 μSv)

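### The arm comparisons named in the protocol are all unadjusted, so precision available from baseline values and season of delivery is given up

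*Protocol*

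**What the plan says.** The statistical item in the protocol's Methods section starts with an analysis of distributions. It then names Student's "T test for normally and U-Mann-Whitney test for non-normally distributed variables", chi-square for categorical variables, and "Pearson or Spearman correlation, one-way analysis of variance or Friedman ANOVA test". P-values "<0.05 were considered significant". No regression, ANCOVA, mixed model or stratified analysis is listed, and no test is tied to a particular outcome or visit.

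Allocation is described in one sentence: "Lactating mothers will be randomly allocated to two groups with different vitamin D intakes". No stratification factor is given. The sample is "150 lactating mother-infant pairs" (Patients).

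On baseline, the visit schedule in Methods says that the assessment "will provide baseline characteristics of the studied participants". Cord blood is taken at delivery, and "Maternal baseline blood samples will be collected within 3 weeks after delivery", at the visit where mother and infant also have DXA. Follow-up is at months 3 and 6.

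On season, the Aim of the study says the trial will "assess the influence of the season of delivery on the maternal" and newborn vitamin D status. Theoretical results states as a hypothesis that such an influence exists.

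**The concern.** The protocol collects a pre-treatment value for most continuous outcomes and names a factor that it expects to drive one of the main ones. It then lists only arm comparisons that ignore both. Where a baseline value predicts follow-up, leaving it out inflates the standard error for no return. Where season affects 25-OHD, a chance difference between arms in season mix passes into the unadjusted difference.

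There is a second, smaller problem. Choosing between t and Mann-Whitney from the observed distribution means that the quantity compared can differ from one variable or visit to the next: a mean difference in one place, a rank comparison in another. Mann-Whitney alone also gives no difference in measurement units.

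At stake is how well 150 pairs can separate the two doses, and how far the observed arm difference depends on the accident of who delivered when.

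**Working it through.** **Inputs from the protocol.** 150 pairs, two arms, significance level 0.05, follow-up at months 3 and 6.

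**Assumptions.** 1:1 allocation (75 per arm) and two-sided tests. Correlation r between baseline and follow-up of 0.3 to 0.7, with equal SD at both times. For season, a difference between half-years of 0.5 to 1.0 SD at the time of comparison. The protocol gives none of these, nor an effect size or power, so there is no figure of its own to reproduce.

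**Step 1: unadjusted comparison.** Detectable difference at 80% power = (1.960 + 0.842) × √(2/75) = 2.802 × 0.1633 = 0.457 SD (0.460 SD by the exact t test).

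**Step 2: adjustment for baseline.** Relative to the plain follow-up comparison, ANCOVA has variance 1 − r² and a change-score t test has 2(1 − r). The detectable difference is 0.457 SD times the square root of the factor.

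| r | ANCOVA factor | Detectable (SD) | n per arm for the same power | Change-score factor | Detectable (SD) |
|---|---|---|---|---|---|
| 0.3 | 0.91 | 0.436 | 69 | 1.40 | 0.541 |
| 0.5 | 0.75 | 0.396 | 57 | 1.00 | 0.457 |
| 0.7 | 0.51 | 0.327 | 39 | 0.60 | 0.354 |
| 0.9 | 0.19 | 0.199 | – | 0.20 | 0.205 |

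The change-score factor exceeds the ANCOVA factor by 2(1 − r) − (1 − r²) = (1 − r)², which is never negative. It is above 1 whenever r < 0.5.

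**Step 3: power at a true difference of 0.4 SD.** With 75 per arm, power is 68.8% unadjusted, against 72.8%, 80.7% and 92.9% with ANCOVA at r = 0.3, 0.5 and 0.7. If only 50 per arm are analysed (assumed), it is 51.6% against 55.4%, 63.7% and 80.0%.

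**Step 4: chance imbalance in season.** With half of the deliveries in each half-year, the SD of the arm difference in season share is √(0.25 × 2/75) = 0.082, or about 8 points. A gap of 10 points or more has probability about 19% if the totals are exactly 75 and 75, and about 22% if each delivery is independently 50:50. A gap of 20 points or more has probability about 2%.

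Given a gap g and a seasonal effect D (in SD), the unadjusted difference is shifted by D × g. Its true standard error is 0.1633 × √(1 − D²/4), while the test uses 0.1633. The type I error conditional on the gap is then:

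| Gap | D = 0.5 | D = 1.0 |
|---|---|---|
| 10 points | shift 0.05 SD, error 5.3% | shift 0.10 SD, error 6.1% |
| 20 points | shift 0.10 SD, error 8.6% | shift 0.20 SD, error 19.8% |

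Averaged over allocations, 20,000 simulated trials with D = 1.0 gave 5.3%. The simulation standard error is √(0.05 × 0.95/20,000) = 0.15 points, so this is about two standard errors from 5%. The level is essentially kept.

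**Step 5: why baseline alone may not be enough for 25-OHD.** Month 6 falls about half a year after the baseline sample. As an illustration, let the seasonal gap be 1 within-season SD and let it reverse by month 6, with within-season r = 0.5. The total variance is 1 + 0.25 = 1.25, and the baseline to follow-up covariance is 0.5 − 0.25 = 0.25, so the overall correlation is 0.25/1.25 = 0.2. Relative to the plain month-6 comparison:

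- Change score: (2 × 0.5 + 1)/1.25 = 1.60.
- ANCOVA on baseline only: 1 − 0.2² = 0.96.
- ANCOVA on baseline and season: 0.75/1.25 = 0.60.

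**The case against.** **The list is a toolbox.** No test is tied to an outcome. A t test on change from baseline is compatible with the list, Friedman ANOVA implies some within-subject use of the visits, and saying that baseline data describe the participants excludes no other use. Covariates are also often left to a SAP. Part of this stands: the protocol does not forbid using baseline, and the missing detail is not the complaint. But every arm comparison it does name is unadjusted, and a change score would bring in baseline without season.

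**The gain could be read as very large for bone and body composition.** At r = 0.9, which a reader might assume for adult DXA, ANCOVA takes the detectable difference from 0.46 to about 0.20 SD. The documents give no correlation, and at that value a change-score t test reaches 0.205 SD against 0.199 SD. The objection stands, and the r = 0.9 contrast should not be used as the size of the fault.

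**A reader might infer that the 25-OHD comparison is biased by season.** It is not. Chance imbalance is already part of the standard error under randomisation, the level holds on average, and a 10-point gap raises the conditional error only to 5.3%–6.1%. The hypothesis in the protocol concerns season of delivery and the status of mother and newborn. Nothing shows that a gap of fixed size, or even fixed direction, persists at months 3 and 6. This also stands, and it is why no seasonal shift in ng/mL is claimed here.

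**Conclusion.** The point holds as one of efficiency and of robustness to the realised allocation, not of validity. That the named arm comparisons are unadjusted, and that the choice between t and Mann-Whitney rests on the observed distribution, can be read directly from the protocol. The size rests on assumptions: 75 per arm, two-sided 5%, and r between 0.3 and 0.7. Under these, 9% to 49% of the variance of the follow-up comparison is left in without need, and the detectable difference is about 0.46 SD where 0.44 to 0.33 SD was attainable. The seasonal element is a further reason to adjust the vitamin D outcomes. Its size is unknown, and it matters materially only for gaps near 20 points, which arise in about 2% of allocations. This is a change that should be made, but the trial would not be invalid without it.

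**What to change.** For the continuous outcomes at months 3 and 6, replace the choice between t and Mann-Whitney with a prespecified ANCOVA or a repeated-measures mixed model over both visits. Include:

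- arm;
- the baseline value of the same variable where one is measured, with cord 25-OHD serving for infant 25-OHD;
- for the vitamin D outcomes, season of delivery or calendar date of sampling.

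The condition on baseline matters, because Methods does not say which analytes are measured in cord blood or whether infants give a baseline urine sample.

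State in advance how skewed outcomes are handled, for example by log transformation, so that the compared quantity does not depend on a normality check. Keep the unadjusted comparison as a sensitivity analysis.

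The cost is analysis wording only. Season is not a listed data item, but it follows from the delivery date and the stated aim already requires it. No visit, sample or participant is added.

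### One-way ANOVA and the Friedman test are offered as alternatives, but they suit different data structures, and neither compares the two doses over time

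*Protocol*

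**What the plan says.** The Methods section of the protocol gives the statistical methods as a single list. It chooses the two-group test by distribution: "T test for normally and U-Mann-Whitney test for non-normally distributed variables". After the chi-square test come two further pairs: "Pearson or Spearman correlation, one-way analysis of variance or Friedman ANOVA test". The last pair, "one-way analysis of variance or Friedman ANOVA test", is assigned to no question or variable. Kruskal-Wallis and repeated-measures ANOVA are not named.

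Two data structures in the trial could call for these tests.

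- **Repeated visits.** "Maternal baseline blood samples will be collected within 3 weeks after delivery", and follow-up "visits will take place at the 3^rd^ and 6^th^ month after delivery". Each participant is therefore measured up to three times, with DXA at each visit.
- **Season of delivery.** The Aim and Theoretical results sections ask whether season affects vitamin D status in mother and newborn. The season groups consist of different women.

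The main comparison is between two arms: "Lactating mothers will be randomly allocated to two groups with different vitamin D intakes". The aim is to "prospectively compare the influence of vitamin D supplementation (400 IU/d vs. 1200 IU/d") on vitamin D status, bone mass and body composition. The Theoretical results section expects that the higher dose "positively changes bone mass and body composition".

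**The concern.** A reader who follows the pattern of the list will take the last pair as one more choice made by distribution: ANOVA if normal, Friedman if not. That rule gives a wrong test in either setting.

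- Across visits, a normally distributed variable would go to one-way ANOVA, which treats three values from one woman as values from three women.
- Across seasons, a skewed variable would go to Friedman, which ranks within matched sets that do not exist.

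There is also a risk of interpretation. Infants grow and mothers recover after delivery whatever the dose, so a change over time within an arm is expected. If it is significant in one arm and not in the other, it is easy to report this as a dose effect. Neither test can show one.

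**Working it through.** The protocol gives 150 pairs and a 0.05 significance level, but no SD, effect size, within-person correlation or power. There is therefore no stated figure to reproduce. Everything numerical below rests on assumptions: 75 per arm (equal allocation), three complete visits, normal data with unit SD, and the same correlation ρ between any two visits.

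**1. Which test fits which question**

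| Question | Data | Parametric test | Rank counterpart |
|---|---|---|---|
| Season of delivery, three or more groups | independent | one-way ANOVA | Kruskal-Wallis |
| Change over three visits | repeated | repeated-measures ANOVA | Friedman |
| Two arms | independent | t test | Mann-Whitney |

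The protocol's pair takes one test from the first row and one from the second. With two arms, one-way ANOVA only repeats the t test (F = t², same P value). It adds nothing there and has no time term.

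**2. One-way ANOVA applied to visits**

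Both F statistics share the between-visit numerator. The repeated-measures error variance is about 1 − ρ, and the one-way error variance is about 1. One-way ANOVA therefore rejects roughly when the repeated-measures F exceeds the one-way critical value divided by 1 − ρ. The one-way critical value on 2 and 222 df is 3.04, and the repeated-measures value on 2 and 148 df is 3.06.

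- No change, ρ = 0.6: the threshold becomes 3.04/0.4 = 7.59, and the chance that F(2, 148) exceeds it is 0.0007. Simulation agrees: type I error is about 0.1% instead of 5%.
- Change of 0, 0.15 and 0.30 SD: the squared deviations from the mean are 0.15² + 0² + 0.15² = 0.045, so the non-centrality is 75 × 0.045/(1 − ρ). This is 8.44 at ρ = 0.6 and 16.9 at ρ = 0.8.

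| ρ | One-way power | Repeated-measures power |
|---|---|---|
| 0.6 | 0.21 to 0.22 | 0.73 |
| 0.8 | 0.11 to 0.12 | 0.96 |

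(The ranges span separate simulation runs and the approximation above.)

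The pattern does not depend on this shape of change. With 0, 0.3 and 0.3 SD at ρ = 0.5, power is 0.38 for one-way ANOVA, 0.76 for repeated-measures ANOVA and 0.61 for Friedman. With no change and ρ from 0 to 0.7, Friedman's type I error is 0.047 to 0.051, so Friedman is valid for visits.

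**3. Friedman applied to seasons**

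Assume four season groups of 37 women and a 0.5 SD shift in two of them. Power is 0.71 for one-way ANOVA and 0.69 for Kruskal-Wallis. Friedman can be computed only by lining women up in arbitrary blocks, and its power then falls to 0.58. With no season effect, all three tests reject in about 5% of runs.

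**4. Within-arm tests read as a dose comparison**

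Assume no dose effect, ρ = 0.5, and the same change (0, δ, δ) in both arms. If p is the chance that Friedman is significant in one arm, the chance that exactly one arm is significant is 2p(1 − p).

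| δ (SD) | p | 2p(1 − p) |
|---|---|---|
| 0.20 | 0.30 | 0.42 |
| 0.25 | 0.45 | 0.49 |
| 0.30 | 0.60 | 0.48 |

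With identical arms, the two within-arm tests would disagree in 42% to 49% of trials.

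**5. What the listed two-group test can do**

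A t test between arms at one visit, 75 per arm, has power of about 0.86 for an assumed 0.5 SD difference.

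**The case against.** The strongest reply is that the protocol never says distribution decides between ANOVA and Friedman. It states that rule only for the t test and Mann-Whitney test. ANOVA may have been meant for season and Friedman for visits, and then neither would be misused. This stands as a possible reading, and it is why the point is one of mismatch on the natural reading and not of certain misuse. It does not remove the defect, because the text does not assign the tests to questions. Under that reading each would also lack the counterpart needed for the other kind of distribution. In the same way, one-way may have been shorthand for one-way repeated measures, but the plain term does not mean that.

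A reader might go further and infer that the dose hypothesis is left untested. The protocol does not support this: the t test and Mann-Whitney test in the same list can compare arms at any visit or on change.

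A reader might also infer that false positive findings over time are likely. The error runs the other way: one-way ANOVA on repeated visits rejects too seldom. Within-arm change is also not itself a stated aim, which limits the harm.

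Finally, a mixed model or a rule for missed visits may be in a statistical analysis plan that is not shown. Their absence is not part of this point.

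**Conclusion.** The point holds in limited form. The protocol offers as alternatives two tests that are not alternatives, and on the natural reading one of them is wrong for visits or for season. For visits the cost is lost power, from 0.73 to about 0.21 at ρ = 0.6 and from 0.96 to about 0.12 at ρ = 0.8, for a 0.3 SD change in 75 women. For season it is a rank test without the blocks that it needs. These sizes depend on assumed correlations, effects and group sizes, none of which the protocol gives. The mismatch itself does not depend on them.

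The more important safeguard concerns interpretation: within-arm time effects must not be offered as evidence for 1200 over 400 IU/d. Severity is moderate, because the misuse is conservative and usable between-arm tests are already listed.

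**What to change.** State which question each test serves, and replace the last pair as follows:

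- **Season of delivery:** one-way ANOVA, with Kruskal-Wallis as the rank alternative.
- **Change across visits:** repeated-measures ANOVA, with Friedman as the rank alternative, described as within-arm and not as evidence on dose.
- **Dose:** a comparison between arms, adjusted for the baseline value that is already collected. Examples are a mixed model for months 3 and 6 with arm, visit, arm × visit and baseline, or ANCOVA at month 6. The adjustment is an improvement on the listed two-group tests, which remain usable.

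The cost is a few lines of wording and standard software. No new data, visits or participants are needed.
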